#### Statistical Analysis of Primary Outcome

Differences in average respiratory minute volume in the first 5 min after birth between the study groups will be tested with a Student's *t*-test if the data are found to be parametric, or with Mann-Whitney u-test when the data are non-parametric.

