### Study Population

The study will take place at the NICU of the Leiden University Medical Center (LUMC) and the NICU of the Amsterdam UMC (AUMC), both located in the Netherlands. Infants with a gestational age between 24^+0^ and 29^+6^ weeks, born at the LUMC and the AMC will be eligible for inclusion. Infants with a congenital abnormality or condition that might have an adverse effect on breathing or ventilation will be excluded, such as congenital diaphragmatic hernia, trachea-esophageal fistula or cyanotic heart disease.

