### Sample Size Calculation

There is no data available on measurements of respiratory effort in the first 5 min after birth during stabilization with a FiO_2_ of 1.0 compared to 0.3. In a recent study, the average minute volume of preterm infants over the first 100 breaths was 150 ± 70 mL/kg/min (30). In a retrospective observational study, we observed an 80% relative increase in respiratory drive when FiO_2_ was switched from 0.21 to 1.0, in the first minute after FiO_2_ was increased (from 134 to 240 mL/kg/min). Other parameters of respiratory effort increased as well: average expired tidal volumes (Vt_e_) increased by 37% (from 4.9 to 6.7 mL/kg), and rate of rise to maximum tidal volumes increased by 32% (13.8 to 18.2 mL/kg/s) (15).

However, since we investigate a FiO_2_ of 0.3 instead of 0.21 in the lower oxygen arm, we expect half of the effect (40% relative increase) in respiratory drive than demonstrated in the study of Van Vonderen et al. (15). Therefore, to detect an increase in average minute volume in the first 5 min after birth from 150 to 210 mL/kg/min, using a standard deviation of 70 mL/kg/min, with a power of 80% and an α error of 5% (two tailed test), 22 infants are required for each arm. Given the fact that parents may withdraw their consent or decline deferred consent after the infant is included in the study, or that the recording of physiological measurements fails in 10% of all infants, a total of 50 infants will be recruited (25 in each arm).

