## Treatment of Subjects

### Randomization

Allocation will be stratified by gestational age. Infants of 24^+0^-26^+6^ weeks and 27^+0^-29^+6^ weeks will be included using variable block (4–6) sizes. Concealment of allocation will be ensured by using the randomization process of Castor EDC (Amsterdam, The Netherlands), an electronic data capture system. The neonatal fellow or neonatal consultant in charge of the procedure will randomize using Castor EDC.

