### Statistical Analysis

Data will be presented as median [interquartile range (IQR)], mean ± standard deviation (SD) or number (percentage) where appropriate. Data will be checked for meeting the assumption of normality first by making a frequency distribution per minute. Outliers will be identified and handled according to the data (outliers will be deleted if there are arguments to do so, or transformed if not). Intention-to-treat will be employed. Statistical analysis will be performed with SPSS software version 23.0 (SPSS, Chicago, Illinois; 2012).

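### The primary test leaves out the gestational-age stratum used in randomisation, and the choice between t-test and Mann-Whitney leaves the effect measure open until the data are seen

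*Protocol article*

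**What the plan says.** Under Randomization, the protocol article states "Allocation will be stratified by gestational age", with bands of 24+0 to 26+6 and 27+0 to 29+6 weeks. Centre is not named as a stratification factor.

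Under Statistical Analysis of Primary Outcome, it states "Differences in average respiratory minute volume in the first 5 min after birth between the study groups will be tested with a" Student's t-test for parametric data and a Mann-Whitney test otherwise. No covariate appears.

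The choice between the two rests on the general Statistical Analysis section: "Data will be checked for meeting the assumption of normality first by making a frequency distribution per minute". No criterion is given. The primary outcome is one value per infant, the average over the first 5 minutes.

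The Sample Size Calculation is in terms of means: the stated aim is "to detect an increase in average minute volume in the first 5 min after birth from 150 to 210 mL/kg/min". It takes the SD as 70 mL/kg/min and concludes that "22 infants are required for each arm".

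Statistical Analysis of Other Outcomes allows adjustment only for characteristics that turn out to differ significantly and relevantly between arms, and only in the linear mixed model. The section on secondary outcomes assigns that model to the time-course and biomarker analyses.

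**The concern.** Stratified allocation balances the arms on gestational age, so the difference between arms varies less from trial to trial than under simple randomisation. An unadjusted test does not credit this. It leaves the between-stratum variance in its error term, so if gestational age predicts minute volume the standard error is too large, the interval too wide and the test below its nominal 5% level.

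The data-driven choice of test raises a separate issue. A t-test addresses a difference in means; a Mann-Whitney test addresses rank ordering. Until the data are inspected, nobody can say which the trial will report. The inspection described concerns per-minute values, whose distribution can differ from that of the 5-minute averages.

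At stake are precision that the design makes available at no cost in infants, and a primary effect measure fixed in advance.

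**Working it through.** **Inputs from the protocol:** difference 210 − 150 = 60 mL/kg/min; SD 70 mL/kg/min; two-sided α 5%; power 80%; 22 evaluable per arm; 10% loss; two strata.

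**Assumed, not in the protocol:** R², the share of within-arm outcome variance explained by the stratum, at 0, 0.10 and 0.20; 11 infants per arm in each stratum; normal errors; total SD held at 70.

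**1. The plan's own figure.** n per arm = 2 × (1.96 + 0.842)² × 70² / 60² = 21.4, so 22. With 10% loss, 22 / 0.9 = 24.4, so 25 per arm and 50 in total. Both reproduce. The noncentral t distribution gives 79.3% power at 22 per arm, a rounding-level difference from 80%.

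**2. Standard error.** The unadjusted test works with 70 × √(2/22) = 21.1. Under stratified allocation the actual value is 21.1 × √(1 − R²):
- R² = 0.10: 20.0, so the unadjusted interval is too wide by a factor 1/√0.90 = 1.054.
- R² = 0.20: 18.9, a factor 1/√0.80 = 1.118.

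**3. Type I error of the unadjusted test.** Large-sample approximation: 2 × [1 − Φ(1.96/√(1 − R²))].
- R² = 0.10: 1.96/0.949 = 2.07, giving 3.9%. Simulation gives 3.8 to 3.9%.
- R² = 0.20: 1.96/0.894 = 2.19, giving 2.8%. Simulation gives 2.7 to 3.0%.

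The stratum-adjusted model stays at about 5%.

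**4. Power at 22 per arm for a difference of 60** (simulation; adjusted values agree with the noncentral t on residual SD 70 × √(1 − R²), one further degree of freedom lost):

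| R² | Unadjusted t-test | Adjusted for stratum | Gain |
|---|---|---|---|
| 0 | 79.3% | 79.3% | none |
| 0.10 | 80.2 to 80.5% | 83.3 to 83.5% | about 3 points |
| 0.20 | 81.5% | 87.3% | about 6 points |

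The right comparator is the unadjusted power at the same R², not 79.3%, because stratified allocation already helps the unadjusted test a little.

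**5. Effect of the switch between tests.** The protocol gives no criterion, so a Shapiro-Wilk test per arm at 5% was assumed.
- Normal outcome: the switched procedure has α 5.0% and power 78.9%, against 78.8% for the t-test alone.
- Log-normal outcome, control mean 150 and SD 70, shift 60: the procedure goes to Mann-Whitney in about 73% of trials, with α 5.3% and power 88.1%, against 79.6% for the t-test alone. The two tests disagree on significance in about 11% of trials.

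The switch therefore does not lose power in these settings. What it does is let the observed data decide which quantity is tested.

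**The case against.** The strongest reply is that nothing planned fails. The 22 per arm were computed for a plain two-group comparison and reproduce. An omitted stratification factor makes the test conservative, not invalid. The size of the loss depends on an R² that the protocol does not give, and the outcome is already divided by body weight, which may remove part of any gestational-age effect. All of this stands, and it limits the point to efficiency and clarity.

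A second reply is that the section on other outcomes already provides for adjustment. It does not meet the point. That route depends on significance tests of baseline differences, which stratification makes unlikely for gestational age, and it lies in the mixed model rather than the primary test. Nor can the matter be left to an analysis plan that is not shown, because the article states the primary test itself.

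A third reply is that the rank test is useful when minute volume is skewed. That is true, and it is a reason to keep one as a sensitivity analysis.

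Some stronger readings are not supported:
- *The normality check costs power.* In step 5 it does not, and with skewed data it gains power.
- *The trial is undersized.* The loss is relative to an adjusted analysis, not to the stated 80%.
- *Centre must also be in the primary model.* Centre is not a stratification factor. The alternative devices are not tied to centres, and the two oximeter makes record saturation and heart rate, not minute volume.
- *The strata were chosen because maturity predicts breathing.* The Randomization section gives no reason.

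**Conclusion.** The point holds as a recommended improvement, not as the correction of an invalid analysis. The primary test ignores the factor on which allocation was stratified. For an assumed R² of 0.10 to 0.20, that makes the interval about 5 to 12% wider than needed, takes true type I error down to about 3.8% and 2.7%, and gives up about 3 to 6 points of power. At R² = 0 nothing is lost by the plan and nothing material by adjusting. That the stratum is absent from the primary test is certain from the text; the size of the effect is conditional on R².

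The mismatch between the per-minute check and the 5-minute average, and between the Mann-Whitney branch and the mean difference of 60 used for sizing, also follows from the text. Its consequence is an open effect measure and room for analyst discretion.

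**What to change.** Prespecify one primary analysis: a linear model of each infant's 5-minute average minute volume per kg on arm and gestational-age stratum, reporting the adjusted mean difference with its 95% confidence interval. Use ordinary model-based standard errors. If robust ones are preferred, name a small-sample version, because with 44 infants the versions behave differently: in simulation HC0 with a normal critical value had 6.8 to 6.9% type I error, HC3 about 4%, and HC1 held 5%.

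Drop the normality-based choice of test and keep a stratified rank test as a sensitivity analysis. Put the stratum into the secondary models as a fixed rule, replacing the adjustment triggered by significant baseline differences. Centre may be added as an optional further covariate.

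The cost is a change of wording and one degree of freedom, or two with centre. At R² = 0, power with both terms is 79.2% against 79.3% unadjusted. No further infants or measurements are needed.

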#### Statistical Analysis of Secondary Outcomes

- The interaction of respiratory minute volume, tidal volumes, rate of rise to maximum tidal volumes and diaphragm activity in the first 5 min after birth with time will be analyzed with a linear mixed model, in which both study group (treatment) and time will be taken in consideration.- Differences in average tidal volumes, average rate of rise to maximum tidal volumes, and percentage of recruitment breaths will be tested with a Student's *t*-test if the data is found to be parametric, or with Mann-Whitney *u*-test when the data is non-parametric.- The concentration of 8-iso-prostaglandin F2α will be analyzed with a linear mixed model, in which both study group (initial FiO_2_ 0.3 vs. 1.0) and time will be taken in consideration.

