### Secondary Outcomes

Secondary outcomes include;

- Average tidal volumes in the first 5 min after birth- Average rate of rise to maximum tidal volumes in the first 5 min after birth- Percentage of recruitment breaths with tidal volumes above 8 mL in the first 5 min after birth- Duration of hypoxia (defined as oxygen saturation < 25th percentile of the target ranges defined by Dawson et al.) in the first 10 min after birth- Duration of hyperoxia (defined as oxygen saturation > 95%) in the first 10 min after birth- Changes in diaphragmatic activity in the first 5 min after birth- Incidence of intubation in the delivery room- Concentration of 8-iso-prostaglandin F2α (29), an oxidative stress metabolite associated with hyperoxia in blood.

Volumes measured will be normalized for body weight. In addition, the interaction between those primary and secondary outcomes and the time after birth will be assessed.

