##### Measurement of metabolites of oxidative stress in blood

Chemical oxidation products of polyunsaturated fatty acids, formed by peroxidation initiated by free radicals, are shown to be the best biomarkers to assess oxidative stress in humans. Of oxidized fatty acids, the best indicator for oxidative stress is 8-iso-prostaglandin F2α (31). Cord blood 8-iso-prostaglandin F2α is a stable marker of lipid peroxidation at birth, and will therefore be analyzed as baseline value for oxidative stress obtained after birth (32).

Measurement time points:

- Cord blood will be drawn directly after birth as a baseline value.- At ~1 h after birth, a blood sample will be taken together with the sample normally taken for measuring standard analyses; this ensures that the infant is not exposed to an extra venepuncture or capillary puncture. The total amount of inspired oxygen given from birth will be recorded from birth until the sample is taken.- At 24 h after birth, again together with measurement of standard blood analyses.

For every sample, a total of 300 μL blood will be used to measure 8-iso-PGF2α. A preterm infant of 500 gram has ~40 mL of total blood volume, whereas an infant of 1,000 gram has ~80 mL. As only 2 samples will be taken from the preterm infants, only 600 μL of blood will be withdrawn, which accounts for 0.75–1.5% of total blood volume.

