A FiO_2_ of 1.0 should be administered with caution to avoid the detrimental effects of hyperoxia (21, 23, 24). However, in this study the amount of time that infants receive pure oxygen is very limited since FiO_2_ will be titrated according to SpO_2_ values. To evaluate pure oxygen exposure, both the amount of time that infants spent above SpO_2_ target range and the level of 8-iso-prostaglandin F2α indicating oxidative stress will be measured.

While low SpO_2_ values reflect a low oxygenation level in arterial blood, known as hypoxaemia, this does not necessarily represent low oxygen uptake and usage by tissues, particularly cerebral tissues. While pO_2_ gradients drive oxygen diffusion into tissues and pO_2_ levels in blood are related to blood SpO_2_ levels, there are any factors that determine oxygen uptake and usage by tissues. For instance, organs can increase blood flow to maintain oxygen delivery and/or increase oxygen extraction when blood oxygen content decreases. As such, SpO_2_ alone provides limited information on oxygen consumption by tissues at high or low blood oxygen levels. In addition, individual patients might differ from one another in their ability to cope with free radicals released in response to inflammation, hyperoxia, and hypoxia before or after birth (21). Although the study is not powered to detect a difference in oxidative stress, we decided to objectively measure this using 8-iso-prostaglandin F2α as marker of oxidative stress, which indicates the true amount of oxygen exposure.

The reported trials comparing high vs. low levels of oxygen did not report on how oxygenation levels influence respiratory effort. Although the level of respiratory support during stabilization at birth was reported in most trials and shown to be not significantly different, the effectiveness of spontaneous breathing in both infants receiving higher or lower FiO_2_ was not evaluated (18, 37–40). Gaining an adequate level of spontaneous breathing during stabilization at birth to improve the success of non-invasive respiratory support could potentially lead to a lower incidence of intubation and mechanical ventilation in the delivery room, contributing to a lower risk of lung injury in high-risk preterm infants.

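### The mixed model for 8-iso-prostaglandin F2α names study group and time but gives the cord-blood baseline no stated role in estimating the treatment effect

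*Protocol article*

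**What the plan says.** The section on measuring oxidative stress metabolites sets three sampling times. The first is before exposure: "Cord blood will be drawn directly after birth as a baseline value". The other two follow it: "At ~1 h after birth, a blood sample will be taken together with the sample normally taken for measuring standard analyses", and "At 24 h after birth, again together with measurement of standard blood analyses". The same section says that the cord-blood value "will therefore be analyzed as baseline value for oxidative stress obtained after birth".

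Under Statistical Analysis of Secondary Outcomes, the concentration goes into a "linear mixed model, in which both study group (initial FiO_2_ 0.3 vs. 1.0) and time will be taken in consideration". No baseline term and no target contrast are named. The first bullet of that section covers "The interaction of respiratory minute volume, tidal volumes, rate of rise to maximum tidal volumes and diaphragm activity" with time, and the marker is not on that list.

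The Secondary Outcomes section, which lists the marker, adds that "the interaction between those primary and secondary outcomes and the time after birth will be assessed". The Discussion concedes the limits of this outcome: "Although the study is not powered to detect a difference in oxidative stress".

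**The concern.** Cord blood reflects the infant before stabilisation starts, so the randomised FiO2 cannot affect it. Such a sample is most useful as a covariate, or as a baseline whose mean is held equal in both arms. The analysis section names neither use, although the measurement section calls the sample a baseline.

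Two things can follow, depending on how the sentence is carried out:

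- **Main effects of group and time over all three samples.** The group coefficient averages one time point with no possible effect and two that carry information. A chance difference in cord blood also enters that coefficient.
- **A group-by-time term with cord blood as an ordinary response.** The later contrasts are unbiased but use the baseline either not at all or with too large a weight.

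The Discussion relies on this marker, together with time above the saturation target, to judge oxygen exposure from starting at FiO2 1.0. An attenuated or imprecise estimate would make an inconclusive result look more reassuring than it is.

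**Working it through.** **Inputs from the document.** Three samples per infant. The Sample Size Calculation requires 22 infants per arm for the primary outcome. That figure reproduces: 2 × 70² × (1.960 + 0.842)² / 60² = 21.4, rounded up to 22. It serves here only as a plausible analysed number. The document gives no effect size, SD or correlation for 8-iso-prostaglandin F2α, so there is no planned figure for this outcome to reproduce.

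**Assumptions.** Complete triplets, equal variance s² at each time, the same correlation ρ between any two samples, no effect at cord blood, an equal effect δ at 1 h and 24 h, two-sided 5% test, normal approximation. Effects of 0.8 SD and 0.5 SD are shown, with ρ from 0.2 to 0.7.

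**Expected estimate and variance of the arm contrast**

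1. Main effects over three samples: estimate (0 + δ + δ)/3 = 2δ/3; variance (2s²/n)(1 + 2ρ)/3. If the effect exists only at 1 h, the estimate is δ/3.
2. Mean of the two later samples, unadjusted: estimate δ; variance (2s²/n)(1 + ρ)/2.
3. Mean of the two later samples minus cord blood: estimate δ; variance (2s²/n)[(1 + ρ)/2 + 1 − 2ρ] = (2s²/n)(1.5 − 1.5ρ).
4. Mean of the two later samples, adjusted for cord blood: estimate δ; variance (2s²/n)[(1 + ρ)/2 − ρ²].

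Power is Φ(estimate/SE − 1.96), with 2/n = 2/22 = 0.0909.

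**Worked example, δ = 0.8 SD, ρ = 0.3**

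- Main effects: 0.533 / √(0.0909 × 0.533) = 0.533/0.220, power 68%.
- Later samples, unadjusted: 0.8 / √(0.0909 × 0.65) = 0.8/0.243, power 91%.
- Change from cord blood: 0.8 / √(0.0909 × 1.05) = 0.8/0.309, power 74%.
- Adjusted: 0.8 / √(0.0909 × 0.56) = 0.8/0.226, power 94%.

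**Power at 0.8 SD, 22 per arm**

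| Analysis | ρ = 0.3 | ρ = 0.5 | ρ = 0.7 |
|---|---|---|---|
| Main effects, three samples | 68% | 58% | 51% |
| Later samples, unadjusted | 91% | 87% | 82% |
| Change from cord blood | 74% | 87% | 98% |
| Adjusted for cord blood | 94% | 96% | 99% |

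**Power at 0.5 SD, 22 per arm**

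| Analysis | ρ = 0.2 | ρ = 0.5 | ρ = 0.7 |
|---|---|---|---|
| Main effects, three samples | 37% | 27% | 24% |
| Later samples, unadjusted | 57% | 48% | 44% |
| Adjusted for cord blood | 60% | 65% | 79% |

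Against the unadjusted later samples, adjustment cuts the variance by 7%, 33% and 58% at ρ = 0.2, 0.5 and 0.7.

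**Simulation check.** In 150 simulated trials with a true later effect of 0.80 SD and ρ = 0.5, the main-effects model gave 0.52 on average (theory 0.53). The group-by-time model gave 0.76 at both 1 h and 24 h (theory 0.80, within simulation error). The interaction term therefore removes the dilution.

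**The case against.** A reader might infer that the plan commits to a main-effects model over all three samples and so builds in a one-third dilution. The document does not support that. Saying that group and time are considered does not mean that only their main effects are fitted. Nearly the same phrase describes the respiratory models, whose stated purpose is an interaction with time. The measurement section says cord blood is analysed as a baseline, which speaks against treating it as just another response. The Secondary Outcomes section foresees assessing an interaction with time for the outcomes it lists, and this marker is one of them. All of this stands, so the dilution is one possible reading and not the stated plan.

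It can also be said that covariates and contrasts for a secondary biomarker are commonly left to the full protocol or analysis plan. That stands in part and lowers the weight. It does not dispose of the point, because the article does name the model and its terms, and they leave out the baseline role that the article assigns elsewhere. The interaction term cures the dilution but not the loss of precision, and it does not say which contrast is the treatment effect.

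Finally, the power figures rest on assumed effects and correlations, and the widest gap sets the least favourable reading against the best alternative. That is fair. The relevant gap, with an interaction fitted, is smaller.

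**Conclusion.** The point holds in a limited form: the analysis sentence gives the cord-blood baseline no explicit role in estimating the treatment effect and fixes no contrast.

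- **If read as main effects over all samples,** the group term recovers two thirds of an equal later effect, or one third of an effect confined to 1 h. This is conditional on a reading that the document does not state.
- **If a group-by-time term is fitted with cord blood as an unconstrained response,** nothing is diluted, but precision is lost. At 0.8 SD and ρ from 0.3 to 0.7, power is about 82–91% (unadjusted) or 74–98% (change from cord blood), against 94–99% adjusted. At 0.5 SD and ρ from 0.2 to 0.7, it is about 44–57% unadjusted against 60–79% adjusted.

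The loss can be as small as one or two percentage points at the favourable end (change from cord blood at ρ = 0.7 and 0.8 SD) or about 35 points (unadjusted at ρ = 0.7 and 0.5 SD). It depends on the assumed effect and correlation, and on equal correlations and complete samples. The primary outcome and the sample size are unaffected. The weight is low: this is a free improvement to a secondary outcome that the protocol itself says is not powered.

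**What to change.** State that the 1 h and 24 h concentrations are the responses in the mixed model, with arm, time, arm-by-time and the cord-blood value as covariate. Alternatively, keep all three samples as responses in a constrained longitudinal model with one common baseline mean for both arms, which also retains infants without a cord-blood sample. Name the arm difference at 1 h and at 24 h as the reported contrasts, each with a 95% confidence interval. A log transformation may be chosen if the distribution calls for it, but it is not part of this defect.

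The cost is a change of analysis wording. All samples are already planned, and no infant, blood draw or assay is added.
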